## Abstract

**Background:**

HIV-associated tuberculosis (TB) co-infection remains an enormous burden to international public health. Post-mortem studies have highlighted the high proportion of HIV-positive adults admitted to hospital with TB. Determine TB-LAM and Xpert MTB/RIF assays can substantially increase diagnostic yield of TB within one day of hospital admission. However, it remains unclear if this approach can impact clinical outcomes. The STAMP trial aims to test the hypothesis that the implementation a urine-based screening strategy for TB can reduce all cause-mortality among HIV-positive patients admitted to hospital when compared to current, sputum-based screening.

**Methods:**

The trial is a pragmatic, individually randomised, multi-country (Malawi and South Africa) clinical trial with two study arms (1:1 recruitment). Unselected HIV-positive patients admitted to medical wards, irrespective of presentation, meeting the inclusion criteria and giving consent will be randomized to screening for TB using either: (i) ‘standard of care’- testing of sputum using the Xpert MTB/RIF assay (Xpert) or (ii) ‘intervention’- testing of sputum using Xpert and testing of urine using (a) Determine TB-LAM lateral-flow assay and (b) Xpert following concentration of urine by centrifugation. Patients will be excluded if they have received TB treatment in the previous 12 months, if they have received isoniazid preventive therapy in the last 6 months, if they are aged <18 years or they live outside the pre-specified geographical area. Results will be provided to the responsible medical team as soon as available to inform decisions regarding TB treatment. Both the study and routine medical team will be masked to study arm allocation. 1300 patients will be enrolled per arm (equal numbers at the two trial sites). The primary endpoint is all-cause mortality at 56 days. An economic analysis will be conducted to project long-term outcomes for shorter-term trial data, including cost-effectiveness.

**Discussion:**

This pragmatic trial assesses an intervention to reduce the high mortality caused by HIV-associated TB, which could feasibly be scaled up in high-burden settings if shown to be efficacious and cost-effective. We discuss the challenges of designing a trial to assess the impact on mortality of laboratory-based TB screening interventions given frequent initiation of empirical treatment and a failure of several previous clinical trials to demonstrate an impact on clinical outcomes. We also elaborate on the practical and ethical issues of ‘testing a test’ in general.

**Trial registration:**

ISRCTN Registry (ISRCTN71603869) prospectively registered 08 May 2015; the South African National Controlled Trials Registry (DOH-27-1015-5185) prospectively registered October 2015.

## Background

HIV-associated TB remains an enormous burden to international public health, even in regions with high coverage of antiretroviral therapy (ART). Globally, in 2014, there were an estimated 0.4 million TB related deaths in people living with HIV, which accounts for approximately one-quarter of TB deaths and one-third of HIV deaths [1]. This burden disproportionately affects sub-Saharan Africa where TB is a common cause of hospital admission and mortality among HIV-positive patients admitted to hospital [2].

Diagnosis of TB in people living with HIV remains challenging due to non-specific clinical features, early dissemination beyond the lungs and relatively low mycobacterial burden within sputum samples [3–5]. A meta-analysis of post-mortem studies in adult HIV-positive patients dying in hospitals in sub-Saharan Africa reported that between 32 and 67 % (pooled summary estimate 43 %) had evidence of TB at post-mortem [6]. TB was disseminated in almost 90 % of patients, and remained undiagnosed at the time of death in almost one-half of TB cases, reflecting a failure of current sputum and clinical based diagnosis of TB, and presenting a strong rationale for routine systematic screening of HIV-positive hospital admissions.

New diagnostic tools have been high on the TB research agenda for the past decade, and are recognised as crucial to the World Health Organization’s (WHO) End TB Strategy [7]. The Xpert MTB/RIF rapid molecular assay (Xpert, Cepheid, Sunnyvale, CA, USA) has a pooled sensitivity for diagnosis of pulmonary TB in HIV-positive adults of 79 % (95 % CI 70–86 %), with 99 % specificity. The test has been approved by WHO and widely implemented in high burden settings [8]. Systematic reviews have also reported very high specificities for Xpert when testing a wide-variety of non-respiratory clinical samples, despite culture being an imperfect reference standard for extra-pulmonary TB [9, 10]. Although data were insufficient for the WHO guidelines to endorse the use of Xpert for TB diagnosis from urine, studies have demonstrated useful diagnostic yield and high specificity in urine among hospitalised HIV-positive patients [11–14].

Urine also has several advantages as a diagnostic sample for hospitalised HIV-positive patients, including relative ease of collection and lower biohazard risk during specimen handling during collection and in the laboratory. The Determine TB-LAM (TB-LAM, Alere, Waltham, MA, USA) lateral flow assay is a simple, point-of-care test for detecting the mycobacterial cell wall antigen lipoarabinomannan (LAM) in urine. It requires 60 μL of unprocessed urine, giving a result in 25 min at a relatively low cost (approximately US$2.50). Whilst sensitivity of this assay is poor in general populations, it is improved in advanced HIV-related immunosuppression, and studies in HIV-positive patients admitted to hospital have demonstrated sensitivities between 40 and 70 % [15–20]. Specificity is exceptionally high when the reference standards include culture of non-respiratory samples [19, 21]. TB-LAM was conditionally approved in November 2015 by WHO for use in diagnosing TB in hospitalised HIV-positive patients [22].

Evidence suggests that high mortality amongst hospitalised patients with HIV/TB co-infection is fuelled by under-diagnosis of TB and delays in diagnosis due to overreliance on sputum based diagnostics, imaging and/or clinical features, and an inability to diagnose disseminated and extra pulmonary TB disease. We therefore sought to evaluate the impact on mortality of a high-yield, rapid-urine based screening approach for TB in HIV-positive medical admissions to hospital in South Africa and Malawi.

### Rationale for studies of clinical impact

A study from South Africa intensively screened unselected HIV-positive hospital admissions to medical wards with comprehensive clinical sampling (sputum, blood, urine and other clinically relevant samples) [14]. Using mycobacterial liquid culture and/or Xpert, TB was diagnosed in 139/427 patients (33 % TB prevalence, 95 % CI 28–37 %). However, only 28 % of microbiologically confirmed TB in this study could have been diagnosed by Xpert testing of sputum alone. In contrast, 81 % of TB cases could have been diagnosed by Xpert testing of both sputum and urine, with additional TB-LAM testing of urine, and results are available within the first 24 h of hospital admission [14, 23]. Xpert is the best diagnostic test available in most high-burden settings and the WHO’s recommended initial TB test for HIV-positive patients. The use of this rapid, relatively low cost screening approach increased diagnostic yield by almost three-fold.

Despite this increase in diagnostic yield, there is no evidence that this urine-based screening strategy will impact mortality or clinical outcomes; it is recommended that impact be demonstrated before such interventions can be endorsed or implemented [24]. This is especially true, as numerous studies have noted that the replacement of sputum smear-microscopy with the more sensitive Xpert has failed to demonstrate any impact on clinical outcomes [25]. A recently published randomised controlled trial of adjunctive urine testing with the TB-LAM assay (the LAM RCT) in a selected population of hospitalised HIV-positive patients being investigated for TB demonstrated an absolute mortality reduction of 4 % (95%CI 1–7 %) and a relative reduction in mortality of 17 % (95%CI 4–27 %). These data support the potential for a urine-based screening approach to reduce mortality among unselected HIV-positive in-patients [26].

### Rationale for a Randomized Controlled Trial (RCT)

Whilst a high yield, urine-based screening strategy might benefit this patient population by increasing the number of TB diagnoses and decreasing time to TB treatment, it may also be associated with a range of adverse consequences. A rapid TB diagnosis within the first 1–2 days of hospital admission may divert clinical attention from co-pathologies, and may reduce the likelihood of empirical prescription of antibiotics for occult bacterial infections. Further, despite excellent specificity, this screening approach may lead to some false-positive TB diagnoses and false-positive rifampicin resistance results from Xpert assays, leading to inappropriate use of potentially harmful medication. Although relatively low cost, the implementation of such a screening strategy will require investment of limited health service resources, and may divert resources from other interventions with potentially greater impact on health outcomes.

Although diagnostic tests are routinely implemented on the basis of diagnostic accuracy or effectiveness without assessment of impact on clinical outcomes (e.g. Xpert and rapid malaria diagnostics), their impact on population health is part of a wider cascade of processes including care seeking and initiation of appropriate treatment [27]. Thus, they should be evaluated under such circumstances too, and evidence of diagnostic accuracy alone should not be taken as evidence of impact on patient-appropriate outcomes such as reducing morbidity or mortality [27]. This is especially true of TB diagnostics, as even mycobacterial culture (the most sensitive diagnostic) can have minimal impact on clinical decision to initiate TB treatment [28].

## Methods/Design

### Aim

The principal aim of this trial is to test the hypothesis that the implementation of a rapid, sensitive urine-based screening strategy for TB can reduce all cause-mortality among HIV-positive patients admitted to hospitals in sub-Saharan Africa when compared to current, sputum-based screening.

### Study design

The trial is a pragmatic, individually randomised, multi-country clinical trial with two study arms with 1:1 allocation between arms (Fig. 1). HIV-positive patients randomised to the ‘standard of care’ arm will be screened for TB by testing sputum (if produced by spontaneous expectoration) using the Xpert assay. HIV-positive patients randomised to the intervention arm will, in addition to the standard of care, have a urine sample (if produced) tested for TB using the TB-LAM assay and, following concentration of 40–50mls of urine by centrifugation, the Xpert assay. Patients, the responsible medical team and study team will be masked to the study arm allocation (except for the study statistician, data managers and laboratory technicians). TB screening test results will be communicated to the medical teams responsible for clinical care of the patients (whilst maintaining masking to study arm allocation), but the clinical management decisions informed by the test results, including whether to commence TB treatment, will not be altered by the study team. Beyond collection of TB screening samples, running of assays and issuing of results, the study team will have no involvement in the clinical care of participants.

**Fig. 1 Fig1:**
[figure not shown]
Study design flow diagram

### Study population

The trial will take place at two sites: Zomba Central Hospital, Southern Malawi, and Edendale Hospital, KwaZulu-Natal, South Africa. Both hospitals serve populations with high HIV prevalence and TB incidence.

All new admissions to medical wards who have confirmed HIV-infection (either an existing or new diagnosis), irrespective of antiretroviral therapy (ART) status, will be screened for eligibility. HIV testing of all hospital admissions with unknown HIV-status is recommended as part of national guidelines at both trial sites, and will be supported by study staff where necessary. Eligibility criteria are designed to be as broad as possible. Patients will be eligible for inclusion regardless of reason for medical admission or presence of TB symptoms (unselected), although patients <18 years old, those who have received TB treatment in the preceding 12 months or isoniazid preventive therapy in the preceding 6 months, those unable to provide informed consent or living outside a pre-defined geographical area will be excluded. It is envisaged that recruitment will take place over a period of 24 months, with equal numbers recruited at each study site.

### Study procedures

After obtaining written informed consent from eligible patients, a study nurse will collect data at baseline to determine clinical history, including TB symptoms, past history of TB and HIV care, vital signs and nutritional and performance status. Venepuncture for haemoglobin concentration and CD4 cell count will be conducted and single sputum sample and up to 50mls of urine will be collected from all participants, irrespective of study arm. If sputum and/or urine samples cannot be spontaneously produced, participants will remain in the study but no further samples for TB investigation will be arranged by the study team. However, the responsible medical team will remain at liberty to arrange further TB investigations that are available as standard of care at the study hospital.

A randomisation list stratified by study site using computer generated random block size will be generated. Randomisation will occur at enrolment, but the study team will be masked to study arm allocation. When TB samples (sputum and/or urine) from participants arrive in the laboratory, the study laboratory technician will identify the allocated study arm by opening a sealed envelope marked with the unique participant ID, and determine which samples will be screened for TB. Urine from participants randomised to the standard of care arm will not be tested for TB and will be safely discarded. TB-LAM assays will be read by the laboratory technician and results will be deemed as positive using the grade 1 cut-off on the manufacturer’s reference card. 20 % of TB-LAM assays will read by a second, blinded reader for quality control.

TB screening tests will only be processed during office working hours on weekdays. Once the TB screening tests have been completed (anticipated to be within 24-48 h of sample collection), the results will be issued whilst maintaining masking of the study arm and responsible medical teams (reported as either ‘TB screening test positive’, ‘TB screening test negative’ or ‘TB screening test not done’). Rifampicin resistance results, when available, will also be communicated to the medical teams.

The responsible medical team will receive training on how to interpret the screening tests, including estimated positive and negative predictive values of the screening algorithms in each study arm, and that a negative screening test does not ‘rule out’ TB. The responsible medical team will be at liberty to organise further TB investigations and commence TB treatment as clinically appropriate. Management of HIV will be as per local and national guidelines, including timing of ART initiation. Data on TB investigations, diagnoses (including if microbiologically confirmed or ‘empirical’) and treatment will be collected during follow-up.

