A trial of adjunctive urine testing with the TB-LAM assay in a selected population of hospitalised HIV-positive patients being investigated for TB (the LAM RCT) recently demonstrated a reduction in mortality at 2-months [26]. The STAMP trial differs from this RCT in respect to several factors. Firstly, the inclusion criteria differ in that STAMP is a screening intervention targeting unselected HIV-positive patients admitted to hospital regardless of clinical presentation, and the LAM RCT investigated the TB-LAM diagnostic in hospitalised HIV-positive patients who were presumed to have TB. As such, STAMP has the potential to detect TB among those without any clinical suspicion for TB on hospital entry. Secondly, the STAMP intervention includes the Xpert MTB/RIF assay performed on urine in addition to TB-LAM, whereas LAM RCT evaluated urine testing with TB-LAM alone. This increases the diagnostic yield of the intervention and adds the potential to diagnose rifampicin resistance. Thirdly, the standard of care in the STAMP trial includes Xpert testing of sputum (if produced) at all study sites, whilst the standard of care in LAM RCT varied from easy access to Xpert in South Africa to no access to Xpert in Zimbabwe. Finally, in the STAMP trial but not in the LAM RCT, both study teams and routine medical teams managing patients are masked to the study intervention arm (i.e. which TB screening tests are done).

The rationale for a clinical trial to demonstrate impact prior to implementation is supported by the lack of demonstrable benefit upon patient outcomes of sputum screening using Xpert in HIV-positive patients, despite increases in diagnostic yield compared to sputum smear microscopy [25]. Reasons for the failure of such trials of Xpert sputum testing to demonstrate impact may include lower occurrence of mortality endpoints in populations studies (largely outpatient based studies), high rates of empirical TB treatment and the failure of some positive Xpert results to be translated to TB treatment due to delays between submission of samples and issuing of results. The decision to start TB treatment is complex, and in such trials is likely to be influenced by the premise of the study to reduce undiagnosed, or ‘missed’ TB cases, potentially increasing empirical TB treatment [36].

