These issues have been considered when designing the STAMP trial. For example, in-patient settings have a high mortality, and initiating TB treatment following positive results is more likely to occur when patients are admitted to hospital compared to community settings. Masking of clinicians, investigators and patients to the study intervention arm should reduce any ‘Hawthorne’ effect which could increase empirical TB treatment in the standard of care arm due to clinicians observing higher diagnostic yield in the intervention arm [37]. The use of ‘double-blinding’ in this manner is unusual in assessments of diagnostics, and, to our knowledge, this is the first time it has been used in TB diagnostics. However, a disadvantage of masking is that it might impair the ability of clinicians to make decisions about TB treatment in the absence of a positive screening result.

The STAMP trial sites have also been chosen to represent differing facilities, cadre of healthcare workers and resource utilisation in the region. Two studies to date, including one RCT, have demonstrated decreases in early mortality from expedited TB treatment in hospitalised HIV-positive patients, supporting the STAMP trial hypothesis that urine-based screening could reduce mortality [26, 31].

The unique challenges of ‘testing a test’ have also been considered in the STAMP study design, in particular, regarding the ethics of conducting such a trial. If considering the diagnostic accuracy or yield of the STAMP study intervention compared to sputum screening or clinical diagnosis alone, [14] it could be argued there is a lack of equipoise (i.e. disagreement about the relative merits of the intervention). Whilst equipoise may not exist for diagnostic accuracy of the intervention for detecting HIV-TB, equipoise clearly exists for the impact of the study intervention on early mortality in unselected HIV-positive hospital admissions when compared to the sputum and clinical screening strategies that are current standard of care [27]. We have also considered the potential negative consequences of a rapid microbiological TB diagnosis, such as delay in initiating ART, a reduction in the prescription of empirical antibiotics which may treat covert sepsis in this severely immunosuppressed population and false-positive rifampicin resistance results. This study will be able to describe and document the impact of these potential harms and compare these secondary endpoints between study arms.

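### The three-way result report separates the arms for participants who give urine but no sputum, so masking is partial rather than complete

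*Protocol article*

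**What the plan says.** **Who is tested on what** (protocol article, Study design). Standard-of-care participants "will be screened for TB by testing sputum (if produced by spontaneous expectoration) using the Xpert assay". Intervention participants get the same and, in addition, "have a urine sample (if produced) tested for TB using the TB-LAM assay", plus Xpert on concentrated urine.

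**What is collected** (Study procedures). A "single sputum sample and up to 50mls of urine will be collected from all participants, irrespective of study arm". Urine from standard-of-care participants is discarded untested. "If sputum and/or urine samples cannot be spontaneously produced, participants will remain in the study", and the study team arranges no replacement sample.

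**What is reported** (Study procedures). Results are "reported as either ‘TB screening test positive’, ‘TB screening test negative’ or ‘TB screening test not done", and the same sentence says that masking is kept.

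**Who is to be masked, and why.** Study design lists patients, the responsible medical team and the study team, with the statistician, data managers and laboratory technicians as exceptions. The Discussion presents it as a strength over the earlier randomised trial of adjunctive urine TB-LAM that "both study teams and routine medical teams managing patients are masked to the study intervention arm". It then gives the purpose: "Masking of clinicians, investigators and patients to the study intervention arm should reduce any" Hawthorne effect that could raise empirical TB treatment in the standard-of-care arm.

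**The concern.** The masking statement and the testing rules cannot both be true for everyone. If the only sample is urine, there is something to test in one arm and nothing in the other, and the report form has a separate category for nothing tested.

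The trial relies on masking to keep empirical TB treatment from depending on the arm. The Discussion names high rates of empirical treatment among the reasons why earlier trials of sputum Xpert may have shown no clinical effect. The leak falls where sputum testing contributes nothing and urine testing makes the whole difference between the arms. Some secondary outcomes are directly exposed. Clinically diagnosed TB is defined partly by the clinical team's decision to treat, and time to TB treatment and use of antimicrobials are also clinicians' choices. All-cause death is an objective endpoint, but care that differs because the arm is known could still change it.

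**Working it through.** The article states no figure on this point, so there is none to reproduce. The check lists every sample pattern under the article's own rules.

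**Step 1. Possible reports by samples given**

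| Sputum | Urine | Standard of care | Intervention | Arm revealed? |
|---|---|---|---|---|
| yes | yes | positive or negative | positive or negative | no |
| yes | no | positive or negative | positive or negative | no |
| no | no | not done | not done | no |
| no | yes | not done | positive or negative | **yes** |

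In three patterns the two arms can produce the same reports. In the fourth they share none.

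**Step 2. Allowing for failed assays.** The article does not define *not done*. Suppose that failed urine testing in the intervention arm is also reported that way, with probability f (assumed 1% to 5%). With 1:1 allocation, for a urine-only participant:

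P(standard of care | not done) = 0.5 × 1 / (0.5 × 1 + 0.5 × f) = 1 / (1 + f)

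- f = 0.01: 1/1.01 = 0.99
- f = 0.05: 1/1.05 = 0.95

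A *positive* or *negative* report still means intervention with probability 1.

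**Step 3. A reader who does not know which samples were given.** Let s be the share producing sputum and u the share producing urine, taken as independent. Neither is in the article; the assumed ranges are s = 0.3 to 0.7 and u = 0.90 to 0.99.

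P(standard of care | not done) = (1 − s) / [(1 − s) + (1 − s)(1 − u)] = 1 / (2 − u)

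- u = 0.90: 1/1.10 = 0.91
- u = 0.99: 1/1.01 = 0.99

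P(intervention | positive or negative) = [1 − (1 − s)(1 − u)] / {[1 − (1 − s)(1 − u)] + s}

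- s = 0.7, u = 0.90: 0.97/1.67 = 0.58
- s = 0.3, u = 0.99: 0.993/1.293 = 0.77

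Both compare with 0.50 before the report. Under these assumptions *not done* says a good deal about the arm even to such a reader; a result says less.

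**Step 4. Who can decode the report.** Study design makes sample collection a task of the study team, which is meant to be masked. Under Study procedures, the medical team is trained on the predictive values of the screening algorithm in each arm, so it knows that the arms differ in testing. The article does not say whether the ward sees which samples were produced; that is plausible, not stated.

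**The case against.** **The leak is confined to one pattern.** This stands. A reader might infer that masking fails for the whole trial. It does not: three of the four patterns stay masked, and the Discussion claims only that masking should reduce the Hawthorne effect, which partial masking can still do.

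**Ward knowledge of sputum production is not stated, and the study team has no part in clinical care.** This stands as a limit on certainty. Inference by study staff does not by itself change treatment. It does contradict the claim that they are masked, and they collect the data on TB investigations, diagnosis and treatment.

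**Some of the feared behaviour is the strategy at work.** Responding to a negative urine result, or treating a patient who has no result, needs no knowledge of the arm and belongs to a pragmatic effect. This is fair. The bias is only the part of care that depends on knowing the arm. In the urine-only group report and arm almost coincide, so data cannot cleanly separate the two.

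**Size.** A reader might divide the 28% of confirmed TB diagnosable by sputum Xpert alone by the 79% pooled sensitivity, get 0.35, and conclude that about 65% of participants had no sputum. The documents do not support this. The 28% is a share of TB confirmed on any sample, and the 79% refers to pulmonary TB. Both concern TB cases, not all participants, and having no sputum is not the same as having urine but no sputum.

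**Rifampicin.** A reader might also take a positive report without a rifampicin result as proof of a positive on TB-LAM alone, hence of the intervention arm. The article says only that rifampicin resistance results are passed on when available, not that every Xpert positive carries one. This is at most a suggestive further leak.

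**The full protocol may hold a safeguard.** It may. The point here is what the article states: a masking claim that its own reporting rule contradicts for one group.

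**Conclusion.** The point holds for participants who give urine but no sputum. For them *positive* or *negative* occurs only in the intervention arm, and *not done* means standard of care except after a failed assay. The masking described in Study design, Study procedures and the Discussion is not achieved for this group among people who know which samples were given.

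How many participants this affects is unknown, and no count should be stated. The probabilities above rest on assumed failure and sample-production rates; the table does not. Nor do the documents fix the direction or size of any effect on mortality. The exposure is arm-dependent empirical TB treatment and the outcomes that clinicians drive, with mortality affected only through care.

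**What to change.** 1. **Restate masking as partial** in Study design, Study procedures and the Discussion, naming the urine-only group. Cost: a text change.
2. **Pre-specify a comparison by arm of empirical TB treatment and of the primary outcome, by sputum produced versus not produced.** Allocation is disclosed only when the technician opens the envelope after samples reach the laboratory, so sputum production is fixed before then and is a valid subgroup variable. It is not among the subgroups listed under Statistical analysis; if the separate analysis plan already has it, a cross-reference suffices. Cost: one more subgroup, using data that sample collection should already supply. It will describe a difference in the no-sputum group but not fully attribute it to knowledge of the arm.
3. **Reconcile the report categories with the masking statement.** One option is a single neutral wording for *negative* and *not done*. Its downsides: clinicians could no longer tell a tested negative from an untested patient, which adds to the disadvantage of masking that the Discussion already concedes; recruitment began in October 2015, so it helps only later enrolments and creates two reporting regimes; and positives without sputum stay unmasked. If the investigators keep the three categories for these reasons, items 1 and 2 still apply.
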